### Measures

Mental health-related knowledge will be measured by the Mental Health Knowledge Schedule [MAKS] [34]. The MAKS comprises six items that cover stigma-related mental health knowledge areas: help seeking, recognition, support, employment, treatment, and recovery, and six items regarding classification of various conditions as mental illnesses. The scale has been tested and found to have good psychometric properties [34]. The total score is calculated so that higher MAKS scores indicate greater mental health knowledge.

Attitudes to mental illness and psychiatry will be measured with the Mental Illness Clinicians’ Attitudes (MICA2) scale [35]. This 16-item scale was developed with input from mental health service users, carers, medical students and trainee psychiatrists, and tested with medical students. The scale assesses stigmatising attitudes to both people with mental illness and to the medical speciality of psychiatry. Psychometric testing of the scale showed good internal consistency and test-retest reliability [35].


### Empathy

The Medical Student version of the Jefferson Scale for Empathy (JSE-S) is a 20 item scale with well-established psychometric properties [38, 39] and is available in multiple languages. Each item has a 7 point Likert scale and the total score ranges 7–140.

### Intergroup anxiety

We will employ Stephan and Stephan’s 12 item intergroup anxiety measure modified for medical students [40]. The scale asks respondents to rate how much they experienced a range of feelings (anxious, apprehensive, comfortable, secure, worried, calm, confident, awkward, tense, carefree, nervous, and at ease) from 0 = not at all to 4 = extremely. A score is created by reverse scoring the positive feelings and averaging all the items.

### Sample size

Using the MAKS, the overall change in score at the first follow up point in a previous study [14] using a medical student sample was 1.91. The standard deviation for the MAKS varies among samples but is typically below 3. Using a standard deviation of 2.89 from one sample gives an effect size of 0.66, and including a dropout rate of 10%, a power level of 90% is achieved with a sample size of 448 in each group. This sample size will be achieved if each of the 25 sites recruits on average 36 students, with group sizes depending on local teaching arrangements. We are anticipating that some sites will recruit larger samples and others smaller, according to the available resources and size of the medical schools.

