### Control arm

A control arm is important for two reasons. First, to control for any effect of psychiatry training that occurs between the first and second sessions; second, to control for the possible effect of the baseline measures (see below). The control group will therefore be administered all the measures at the same times as the intervention group, i.e. at two sessions during which the intervention group is receiving the training. Alternatively, two separate, consecutive psychiatry rotations may act as the intervention and control groups, if this is feasible. Students will be allocated by the trainer to either the control or the intervention group according to their usual local teaching group allocation at each site.

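### The effect size of 0.66, the 90% power and the 448 students per group do not belong together; 448 matches a 0.66-point difference, not 0.66 SD

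*Protocol article*

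**What the plan says.** The whole calculation is in one paragraph, Methods/design, Sample size. Its steps are:

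- The effect is "the overall change in score at the first follow up point in a previous study", and this change "using a medical student sample was 1.91".
- It is then standardised: "Using a standard deviation of 2.89 from one sample gives an effect size of 0.66".
- After a 10% dropout allowance, "a power level of 90% is achieved with a sample size of 448 in each group".
- The target is to be met by 25 sites recruiting 36 students each on average.

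The paragraph gives no alpha, no intraclass correlation (ICC) and no design effect. Dropout is the only inflation it names. Clustering appears in the Statistical analysis section, which plans a random effects model for sites and countries, but the article does not connect that model to the figure of 448.

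The Control arm section gives, as one reason for having controls, "to control for any effect of psychiatry training that occurs between the first and second sessions". The comparison of interest is therefore between arms.

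**The concern.** An effect size of 0.66 is moderate to large, and a two-arm comparison of means at 90% power needs only some tens of students per group to detect it. A figure of 448 belongs to a much smaller effect. If the inputs and the result disagree, the power statement misreports what the study can detect.

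Two things depend on it. First, readers would take the study as sized for a 1.91-point difference and judge a small or null MAKS result against that. If 448 in fact corresponds to 0.66 points, that yardstick is 1.91/0.66 = 2.9 times too large. Second, the figure sets the average of 36 students per site. The Discussion also plans to ask remaining sites for more students if others drop out, so as to reach the target. Without a correct basis for the target, nobody can judge how much shortfall is tolerable.

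**Working it through.** **Inputs from the Sample size section:** change 1.91; SD 2.89; effect size 0.66; power 90%; dropout 10%; 448 per group, equal groups; 25 sites with 36 students on average.

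**Assumption:** two-sided alpha of 5%, because none is stated. Other values are tried in step 3.

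**Formula:** n per group = 2 (z₀.₉₇₅ + z₀.₉₀)² × SD² / difference², where 2 (1.9600 + 1.2816)² = 21.015. Recruited n = n / (1 − 0.10).

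**1. The effect size.** 1.91 / 2.89 = 0.661. The division is correct, and 0.66 is already in SD units.

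**2. From 0.66 SD to a sample size.** n = 21.015 / 0.66² = 21.015 / 0.4356 = 48.2, so 49 evaluable per group (50 with the t distribution). With dropout, 49 / 0.9 = 54.4, so 55 (56 from the t-based 50). The stated 448 is not reproduced.

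**3. Other readings of the inputs** (recruited per group, 10% dropout included):

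| Variant | Per group |
|---|---|
| one-sided 5% | 45 |
| SD 3 in place of 2.89 | 58 |
| two-sided alpha 0.0167 | 70 |
| two-sided alpha 0.01 | 77 |
| two-sided alpha 0.001 | 107 |
| SD 2.89 × √2 (uncorrelated change score) | 108 |

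None comes near 448.

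**4. Using 0.66 as a raw MAKS difference with SD 2.89.** n = 21.015 × 2.89² / 0.66² = 21.015 × 8.3521 / 0.4356 = 402.9, so 403. Then 403 / 0.9 = 447.8, so **448**, an exact match. Small changes of method move it by one: the unrounded 0.6609 gives 402, then 447; the t distribution gives 404, then 449.

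**5. What 403 evaluable per group can detect (independent students).** The standardised difference detectable with 90% power is √(21.015 / 403) = 0.228, which is 0.228 × 2.89 = 0.66 MAKS points. Power at 0.66 SD is above 99.99%.

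**6. The clustering explanation.** To reach 403 from 48.2 the design effect must be 403 / 48.24 = 8.35. With design effect = 1 + (m − 1) × ICC, this implies:

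- m = 36 (all students at a site): ICC = 7.35 / 35 = 0.21.
- m = 18 (one arm at a site): ICC = 7.35 / 17 = 0.43.

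**7. Recruitment.** 25 × 36 = 900, against 2 × 448 = 896. This step is consistent.

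**The case against.** **The formula is not printed.** Double standardisation is therefore an inference. The exact match also needs particular choices: a normal approximation, two-sided 5%, 0.66 rounded before reuse, and division by 0.9. This is fair, and the point should be put as the most likely explanation. All these choices are conventional, however, and the mismatch in step 2 stands whatever its cause.

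**A condensed article may have left out a design effect.** This cannot be excluded. It would have to be very large, nothing in the paragraph hints at it, and dropout is named as if it were the only allowance. Even then the text would be wrong as written, because it presents 448 as the result of the effect size, the power and the dropout rate alone. The absence of an ICC is not a separate fault here, since an article may leave it to the full protocol.

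**The discrepancy runs in the safe direction.** Before clustering, 448 is more than the stated inputs require, and no analysis depends on the paragraph. This stands. The damage is to what the power statement tells readers and sites.

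**The 1.91 may be a legitimate between-arm figure.** A reader might infer from the word *change* that it is a pre-post shift within one group, and so the wrong quantity for a comparison of arms. The documents do not settle this; only the cited study can. The Control arm section explains why controls are used, not what 1.91 measured. A request for clarification is as far as the point goes.

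**Conclusion.** The power statement is wrong as written. Under an assumed two-sided 5% alpha, 0.66 SD with 90% power and 10% dropout needs about 55 students per group before clustering, against a stated 448. No other alpha or SD tried gave more than 108. Most likely an effect already in SD units was divided by the SD again, which inflates the evaluable number by 2.89² = 8.35. On that reading 448 corresponds to 0.66 MAKS points (0.23 SD) with independent students.

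Two stronger conclusions do not follow. One is that the study is oversized and could be cut to about 55 per group: allocation follows teaching groups and no ICC is given, so the independence calculation is no basis for a reduction. The other is that it is underpowered. Actual power cannot be fixed from the article. As an illustration, with 403 evaluable per group, a true difference of 0.66 SD and 36 students per cluster, power is about 99% at ICC 0.10, 91% at 0.20 and 85% at 0.25.

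**What to change.** Keep the recruitment target and rewrite the paragraph in one of two ways, depending on how 448 was obtained.

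- **If no clustering allowance was included:** state that 448 per group (403 evaluable after 10% dropout) gives 90% power at two-sided 5% for a between-arm MAKS difference of 0.66 points (0.23 SD, SD 2.89) before clustering. Follow this with the detectable difference over a range of assumed ICCs. For illustration, 403 / 25 is about 16 evaluable students per arm per site. Treated as one teaching group, the detectable difference is 0.66 × √(1 + 15 × ICC): about 0.71 points at ICC 0.01, 0.87 at 0.05 and 1.04 at 0.10. These ICCs and the group size are assumptions, to be replaced by the study's own.
- **If 448 did include a clustering allowance:** state the alpha, ICC and cluster size that lead from 0.66 SD to 448.

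In either case, remove the statement that 0.66 SD with 10% dropout alone gives 448. Say whether 1.91 is a within-group change or a between-arm difference; the power statement needs the latter.

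The cost is one reworded paragraph and a look at the cited study. Enrolment, data collection and analysis do not change.

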### Recruitment

Eligible medical students will be those currently undertaking their rotational training in Psychiatry, which takes place in different years of training in different countries. An Information Sheet to eligible medical students will be distributed at least 24 h before the first session via email or by hand at a previous teaching session, and again at the start of the first session; written informed consent will then be sought at the start of the first session. One to one consent will be ensured through the availability of multiple members of the research team who will answer individual students’ queries. Non-participating students will not be able to attend the training, as their receipt of the training without providing data may be perceived as unfair by participating students. It will be made clear to students prior to and at the start of the session that non-participation will not affect students’ future performance on their medical course in any way.

### Procedure for participants and data collection

Once written informed consent has been received, participating students in the intervention group will be given the questionnaire based measures to complete, and will then undertake the OSCE at the start of Session 1. Data collection using the questionnaire based measures and the OSCE will be repeated at the end of Session 2. Students in the control groups will be given the same measures and will carry out the OSCE during the same time frame as the intervention group. Instead of receiving the intervention they will be able to discuss the OSCE feedback with the role player, after the second attempt (Fig. 1).

**Fig. 1 Fig1:**
[figure not shown]
Flow diagram to illustrate the process for study participation

### Data management

Data will be entered locally using a database provided by the research group at the lead site at King’s College London. Pre and post data will be linked using a study ID number and no identifying information will be included. The cleaned, final dataset at each site will be returned to the lead at the King’s College London site for analysis of the whole sample (both intervention and controlled arm). Data collection will be completed by the end of 2018.

All data collection and data entry will be performed by trained research staff. If errors are found in the database, inconsistencies will be clarified by referring to the relevant hard copy. The quality of data collection will be supervised by senior researchers in the site, with overall supervision by the principal investigator. A Microsoft Excel database has been developed to include data type checks and field guidance. Supervisors will monitor data quality, periodically carry out a set of pre-defined quality checks on the data, raise any queries with the relevant staff and identify missing data in the field. Where data are found to be missing, researchers will endeavour to revisit the participant to obtain the missing data. All storage of data will be in accordance with King’s College London’s data protection policy (http://www.kcl.ac.uk/college/policyzone/assets/files/governance_and_legal/DataProtectionPolicy_updated_Oct2011.pdf). All data will be anonymised for analysis and will be accessible to the project investigators, the project co-ordinator and the data entry clerks within the INDIGO Partnership. Identifying data will be kept as a separate list with identifying codes, for the research records. The document linking the project identification number with personal data will only be accessible to the study research team in the country sites, restricted to the project co-ordinator and data entry clerks, and all the anonymised data will be used for analyses.

### Statistical analysis

Total scores for MAKS, MICA2 and the OSCE will be calculated so that a higher total score represents a more favourable outcome. Descriptive summaries of score changes will be calculated between the baseline and follow up time points for each group. Parametric and non-parametric tests will be employed to detect statistically significant differences in means on individual-level data before and after implementation of the intervention compared to the controls. Statistical analyses of individual-level data will be conducted using a random effects model accounting for clustering within sites and countries, to take into account the between country and culture variation in the attitudes towards mental illness. Changes in each outcome will be investigated at baseline and at the follow up time point after the intervention. All models will be adjusted for gender; age (as a continuous variable); country income category (high, middle or low) and familiarity with people with mental health problems (self or other i.e. family member, friend). In order to appropriately quantify the direct and indirect effects of empathy and anxiety on the three outcomes (MAKS, MICA2 and the OSCE), we will conduct a mediation analysis under the causal framework with the use of the g-computation formula, which has been shown to produce reliable estimates in such scenarios (http://aje.oxfordjournals.org/content/early/2014/12/10/aje.kwu239.full.pdf).

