## Discussion

This study applies components found to be effective from medical education research in an anti- stigma training intervention for medical students. It incorporates reflection and self reflection, which has been effective in consolidating learning and improving attitudes in medical education studies [15]. This is particularly relevant as the intervention aims to change attitudes in medical students towards patients with mental illness. The OSCE involves communication and interviewing skills training, and previous work in medical education demonstrated good communication skills lead to greater satisfaction with care in patients [41] In addition studies have shown a decrease in patients’ distress and potential susceptibility to symptoms of depression or anxiety, in response to good interviewing skills [42]. Therefore training students in interviewing skills should lead to patients feeling more able to express concerns regarding anticipated and experienced discrimination in clinical consultations.

This is also the first international study across high, middle and low-income countries, which will evaluate the effectiveness of training for medical students to respond to experienced and anticipated discrimination. The range of sites will provide a valuable contribution to test the feasibility and effect of the training in multiple settings, therefore increasing the validity of any relevant conclusions drawn from the results. In addition this study measures change in skills at addressing discrimination using an OSCE, which is a new contribution to the field of stigma research. Previous studies have mostly focused on measuring change in knowledge and attitudes [11, 12].

As the study is unfunded there is a risk some sites may drop out. In this event we will ask the remaining sites to increase their sample numbers if possible, to achieve the target sample size. Several sites (including the UK) have resources available to do so.

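### The planned simple significance tests carry no site term, so if the READ:control ratio varies between sites they can mix site differences into the READ effect; the random-effects model is much less exposed

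*Protocol article*

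**What the plan says.** The Methods/design section calls the study non-randomised, with 25 medical schools in 15 countries. Under Control arm, the trainer at each site assigns students by their usual teaching group; as an alternative, "two separate, consecutive psychiatry rotations may act as the intervention and control groups, if this is feasible". The Discussion repeats that existing teaching groups are assigned. The Sample size section targets equal totals of 448 per arm and an average of 36 students per site, "with group sizes depending on local teaching arrangements". No ratio of READ to control students within a site is stated.

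The Statistical analysis section then describes, in separate sentences:

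- descriptive summaries of score changes;
- simple tests: "Parametric and non-parametric tests will be employed to detect statistically significant differences in means on individual-level data", comparing READ with control, with no mention of site;
- a model: "Statistical analyses of individual-level data will be conducted using a random effects model accounting for clustering within sites and countries", with fixed adjustment for gender, age, country income category and familiarity with mental health problems.

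Neither the tests nor the model is described as a comparison within sites. On attrition of sites, the Discussion says: "As the study is unfunded there is a risk some sites may drop out".

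**The concern.** Each school supplies its own READ and control students, so the comparison that this design supports is READ against control inside a school. A test that ignores site compares all READ students with all control students. If some schools supply mostly READ students and others mostly controls, the arms differ in their mix of schools. Any difference between schools in how scores change then counts as READ effect.

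The driver is the ratio, not the size: schools of very different size with one common ratio cause no such leak. Taking change from baseline removes stable differences in level between schools but not differences in change. Such differences are plausible, because the Intervention section says that the length of the psychiatry rotation varies by school.

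At stake is bias in the estimate, apart from any problem with its standard error. The simple tests and the model could also disagree for this reason alone.

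**Working it through.** **The plan's own figures.** The Sample size section gives a change of 1.91 and an SD of 2.89; 1.91/2.89 = 0.66, as stated. The 448 per group does not follow from these: at two-sided 5% (assumed) and 90% power, 2 × (1.960 + 1.282)² / 0.661² gives 49 per group, and 49/0.9 gives 55. That is a separate matter and has no bearing here. Used below: 25 sites, 36 students per site, and SD 2.89 to convert to MAKS points.

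**Assumptions, none of them in the documents.** The ICC of the change score between sites is 0.02 to 0.20, with total SD 1, so site-SD = √ICC. In scenario (a), 12 sites split 24 READ : 12 control and lie 0.5 site-SD above the mean; 13 sites split 12 : 24 and lie 0.5 below. There is no true READ effect.

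**Simple test, (a).**
- READ students: 12×24 + 13×12 = 288 + 156 = 444. Mean = (288×0.5 − 156×0.5)/444 = 0.149 site-SD.
- Controls: 12×12 + 13×24 = 144 + 312 = 456. Mean = (144×0.5 − 312×0.5)/456 = −0.184 site-SD.
- Bias = 0.149 + 0.184 = 0.333 site-SD, multiplied by √ICC.

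**Random-intercept model, (a).** The estimate averages a within-site and a between-site comparison, weighted by information (p = a site's READ share, n = 36):
- within: W = Σ n·p(1−p)/(1−ICC) = 25×36×(2/9)/(1−ICC) = 200/(1−ICC);
- between: B = Σ n·(p−p̄)²/(1−ICC+n·ICC). With p̄ = 444/900 = 0.493, the numerator is 36×(12×0.1733² + 13×0.16²) = 24.96;
- between-site slope = (1 site-SD)/(1/3) = 3√ICC;
- bias = 3√ICC × B/(W+B); model SE = 1/√(W+B); within-site SE = 1/√W.

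At ICC 0.10: W = 222.2, B = 24.96/4.5 = 5.55, B/(W+B) = 0.0244, and bias = 0.949 × 0.0244 = 0.023.

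| ICC | Simple-test bias (SD) | Model bias (SD) | Model SE | Within-site SE |
|---|---|---|---|---|
| 0.02 | 0.047 | 0.028 | 0.068 | 0.070 |
| 0.05 | 0.074 | 0.028 | 0.068 | 0.069 |
| 0.10 | 0.105 | 0.023 | 0.066 | 0.067 |
| 0.20 | 0.149 | 0.017 | 0.063 | 0.063 |

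At ICC 0.10 the simple-test bias is 0.105 × 2.89 = 0.30 MAKS points, or 0.105/0.66 = 16% of the planned effect. It passes one within-site SE from about ICC 0.05. The model bias stays below half its SE throughout (largest ratio 0.028/0.068 = 0.42).

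**Scenario (b), one-arm sites.** Five sites contribute 18 READ students and no controls and lie one site-SD low; 20 sites split 18:18. Simple-test bias = −90/450 = −0.20 site-SD, which is −0.028, −0.063 and −0.089 SD at ICC 0.02, 0.10 and 0.20. Model bias is −0.016 to −0.023 SD over ICC 0.02 to 0.20, about a third of its SE or less.

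**Wider spreads.** ICC 0.10, READ share perfectly tied to site mean (a worst case). Bias is in MAKS points; the within-site SE is 0.19 in the first row. False-positive rates come from 150 simulated studies per row, so a 5% rate is uncertain by about 3.5 points.

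| READ share across sites | Bias: simple / model | False positives: simple / model / fixed site |
|---|---|---|
| 1:2 to 2:1 | 0.37 / 0.08 | 40% / 3% / 5% |
| 20 to 80% | 0.66 / 0.15 | 86% / 7% / 5% |
| 10 to 90% | 0.88 / 0.22 | 100% / 19% / 4% |

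With READ share unrelated to site mean there is no systematic bias, but the simple test still rejected in 7%, 10% and 15% of studies for the three spreads, against 3 to 6% for the model.

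**After the fix.** Adding each site's READ proportion to the random-intercept model gives zero bias in (a) and (b), with the same SE as fixed site intercepts: at most about 4% above the model without that term (0.074 against 0.071 in (b) at ICC 0.02). The worst case examined, shares of 10 to 90% at ICC 0.02, costs about 8%.

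These calculations leave out the country effect and the covariates.

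**The case against.** Several points on the other side are sound.

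- **The model is close to a within-site analysis.** With about 36 students per site and both arms present, almost all of its weight is within-site. A reader might infer that a model with random site effects is confounded by site to the same degree as an unstratified test. The figures above do not support that. Nor does the model rest on random effects alone: it adjusts for country income category, which removes part of the country difference.
- **The text does not say that the tests pool sites.** It is silent on stratification, and the abstract names only random-effects models. One could read the tests as preliminary, with their form left to an analysis plan that is not shown. Against this, descriptive summaries have their own sentence, and the tests are given the purpose of detecting significance against controls. As worded, they are inferential and unadjusted.
- **The scenarios are constructed.** Nothing in the documents suggests that READ-heavy schools have larger or smaller changes, and the overall arm targets are equal. It is equally true that nothing in the allocation prevents such a link.
- **One-arm sites are only a possibility.** The article says that sites may leave, not that they leave between rotations or that one-arm data would be analysed.
- **Change scores and income adjustment shrink the relevant ICC.** It is the ICC of change, for which no value is given. The lower end of the range may be nearer the truth.
- **Fixed site intercepts are not needed.** With 25 of them the planned income adjustment could not be estimated, since income category is constant within a site. Random or fixed intercepts is a matter of preference here.

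**Conclusion.** The concern holds for the simple tests. As described they ignore site, in a non-randomised design where the arm ratio may differ between schools. If that ratio is related to a school's change in score, bias of 0.05 to 0.15 SD is possible under 2:1 and 1:2 splits with site shifts of half a site-SD and an ICC of 0.02 to 0.20. Without such a relation there is no systematic bias, though the test's error rate is still too high.

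The random-effects model is a minor matter: about 0.02 to 0.03 SD in the same setting, under half a standard error. It becomes material only if arm imbalance is extreme and tied to site outcome. One-arm sites are the limiting case, and even five of them did not reach that point in scenario (b).

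The documents do not support the stronger conclusion that the READ effect from the planned model is substantially a country or school difference. All sizes rest on assumed ICCs, arm ratios and site shifts.

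**What to change.** In the Statistical analysis section:

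1. State that inference on the READ effect rests on the random-effects model.
2. In that model, keep the random site and country effects and the listed covariates, including income category, and add each site's proportion of READ students among those analysed. The READ coefficient is then the within-site effect.
3. Either stratify the simple tests by site (site-stratified mean difference; van Elteren test in place of an unstratified rank test) or label them descriptive.
4. Say that a site ending with one arm is described but adds nothing to the READ-control contrast.

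This takes a few sentences and no new data. The standard error rises by roughly 0 to 4% in the main scenarios and about 8% with extreme imbalance, and one-arm sites no longer contribute to the effect. The change does not make teaching groups or rotations within a site comparable; that limit of a non-randomised design remains.
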